#### Professionals

The innovation focuses on a professional level, directed to individual hospitals and their key target groups. Key target groups are gynaecologists and anaesthetists involved in gynaecological surgery and nurses of the gynaecology department. Gynaecological oncologists of the tertiary hospitals assist in major ovarian surgery in the regional hospitals that are authorised to perform these procedures. These oncologists are technical experts assisting in the operating room and are not involved in pre- and postoperative care. They are judged to have no influence on the implementation of the programme in the regional hospitals.

#### Patients

Women aged over 18 years and scheduled for elective abdominal surgery for diagnosis and/or treatment of (suspected) ovarian, endometrial, or cervical cancer will be included during the 1-year implementation period. No specific exclusion criteria will be applied.

### Control group

Hospitals randomised to the control group will receive the traditional breakthrough strategy. The breakthrough series will be performed as usual. The CBO will chair the collaborative and recruit an expert panel including subject matter experts and an implementation expert. All participating hospitals will be instructed to appoint a multidisciplinary improvement team to lead the local improvement activities and will be visited by a CBO consultant and the researcher of the project to clarify the collaborative processes and expectations. Three educational sessions will be conducted with 3 months in between (Fig. 2). At the first learning session, the kick-off meeting, the expert team presents the vision of ideal care (the ERAS programme) and shows that actual care deviates from ideal care. The participants are taught an approach for organising and carrying out their improvement activities. This approach is called the Model for Improvement and identifies four key elements of successful process improvement: measurable aims, measures of improvement, key changes that will result in the desired performance, and a series of testing cycles, known as plan-do-study-act (PDSA) cycles [26]. This model enables teams to test change locally and then reflect, learn, and refine the changes. At the second and third learning sessions, teams learn from each other as they report on successes by feeding back their data during the learning sessions, report on lessons learned, and exchange experiences.

**Fig. 2 Fig2:**
[figure not shown]
Overview of the stepped and breakthrough implementation strategy. The diagram shows the structure of the breakthrough strategy (*control group*) with standard iterative plan-do-study-act (PDSA) cycles and the stepped implementation strategy (*intervention group*) with four implementation levels depending on progress. The *light blue colour* represents the intensity of external support

### Intervention group

The intervention group will be exposed to the stepped implementation strategy, which consists of four steps of implementation activities. This strategy is built on the assumptions that for some hospitals a generic improvement approach may be sufficient, while for other hospitals a full-blown breakthrough approach or an even more intensive tailored approach may be required. The four levels of intensity will be offered successively, with 3 months in between (Fig. 2).

#### First implementation level

The first implementation step aims at promoting awareness and comprises a digital toolbox available for the participating hospitals. The toolbox consists of background information of the ERAS programme, a short summary of the programme to use as a reminder in daily care, and a ready-to-use patient information sheet to structure patients’ preadmission counselling and postoperative care. We assume that this toolbox might pave the way to start implementation for those clinical leaders who have the skills to guide their department through this innovation. This assumption is fed by our experience that in the project ‘implementation of short stay in breast cancer surgery’ [27] as well as in the breakthrough project ‘perioperative care’ [28] some hospitals started immediately with treating patients according to the new programme after the programme was disseminated.

#### Second implementation level

The second step is built on support to make change happen via an interactive learning session, provided by experts in the field of implementation and experts in the implementation of the ERAS programme. The overall aim of this national meeting is to learn about the innovation and to increase motivation. The perioperative care elements and the effectiveness and safety of the ERAS programme will be discussed. Results of baseline measurement will be fed back, and the gaps between actual practice and optimal practice will be demonstrated. The subject matters of this educational meeting are comparable to the kick-off meeting in the breakthrough series, but the number of participants is limited to a maximum of three per hospital team to ensure interactive participation, promote leadership, and limit costs.

#### Third implementation level

The third step is, in contrast to the previous one, a regional activity and aims at influencing the views regarding the innovation and creating a positive intention to change. All locally involved professionals will be invited to participate in a regional meeting to learn from each other via exchange of experiences. Professional peers and opinion leaders will be used to convince them that the programme is valuable, effective, useful, and feasible.

#### Fourth implementation level

The fourth level is the most intensive one and acts on the local level. Activities comprise identification of local barriers to change and selecting activities to promote the adoption of the programme. Members of the expert team will conduct outreach visits and will guide the local team through the process of tailoring interventions. Again, audit data will be used to define to what extent the team deviates from best practice. Local cultural and environmental issues that hinder or facilitate the change process will be identified, and implementation activities will be carefully linked to these barriers and facilitators to change.

The decision to step up to a higher level of implementation activities will be based on the success of implementation. The standards of implementation success include the following: at least 80 % of patients recovered within 3 days and at least 60 % of patients going home within 5 days after surgery. Although we expect the hospitals to include about 25 patients per established evaluation period of 3 months, we assume that improvements need some time to get incorporated in routine practice. The final decision on the implementation level will be a shared decision with the hospital, which might have good reasons for clarifying the lack of success or for preferring to step up to a higher level of implementation intensity even though the benchmark of success was reached.

### Outcome measures

Process and clinical outcome data will be measured by predefined indicators of success to study contextual factors that are critical to the change process. An effectiveness, economic, and process evaluation will be conducted throughout the trial.

#### Effect evaluation

The primary outcome measure is length of hospital stay, defined as the number of nights that a patient stayed in hospital after surgery. Secondary outcome measures are length of recovery and guideline adherence. Recovery is defined as the first day after surgery that the patient fulfilled all three discharge criteria: tolerance of food, adequate pain control on oral analgesics, and independency in activities or daily living. The complete ERAS programme, as proposed by the ERAS Society® [2], includes over 20 protocol care elements. Index elements were selected as having a high level of evidence, being readily recordable, or having a direct influence on recovery. Those elements are the following: preadmission counselling, no bowel preparation, carbohydrate load, use of prophylactic antiemetics, removal of nasogastric tube on end of surgery, no peritoneal drainage, start fluids on day 0, start normal food and mobilisation on day 1, use of epidural analgesia, use of laxatives, and urinary catheter removal on day 2. Guideline adherence to the index elements will be registered for all eligible patients during the study period.

#### Economic evaluation and budget impact

An economic evaluation will be performed. Research has shown that ERAS leads to cost savings without compromising patients’ safety or quality of life [29–31]. As neither a difference in health outcomes is expected from implementation of ERAS in gynaecological surgery nor a difference in costs outside the hospital [32] (i.e. productivity costs), the economic evaluation will basically take the form of a cost-minimisation analysis and will be performed from a hospital perspective. The effectiveness of the implementation strategies (length of postoperative hospital stay) can be expressed as costs. Therefore, for both strategies, implementation costs will be calculated and compared with the cost savings due to the reduction in hospital stay. The strategy which returns the lowest net costs is considered to be the most cost-effective.

#### Process evaluation

The quantitative results will be complemented with a process evaluation. Normally, the outcomes for process evaluation are only measured in the intervention arm. In this comparative effectiveness research study, we will also measure the uptake of the implementation strategy in the control arm. The evaluation will provide valuable insights in potential barriers and facilitators that affected the effectiveness of both implementation strategies. Process data will be collected in line with a framework provided by Hulscher et al. to address actual intervention exposure and to describe experiences with the intervention [33]. Implementation fidelity will be monitored by the registration of guideline adherence to the index protocol elements during all phases of perioperative care. The registration of the number and type of professionals involved and the attendance of the educational meetings will be measured. The barriers that emerge during the educational sessions and outreach visits and the solutions to overcome these barriers will be monitored as well. Besides, all communication between the expert and local teams will be registered.

### Data collection

Before the start of implementation activities, a baseline audit of process and outcome data will be performed by reviewing medical charts of the first 30 patients treated in 2012. This period was chosen as the ERAS programme was not discussed yet in the DGOG. In case of an insufficient number of patients, the retrospective audit will be completed with patients operated in 2011. Hereafter, from the first day of the start till the end of the project 1 year later, a member of the expert team will monitor process and outcome data for both the intervention and the control group. An electronic database supporting good clinical practice guidelines will be available. Patient characteristics, process indicators, and outcome measures (proportion of patients reaching functional recovery within 3 days and proportion of patients hospitalised for a maximum of 5 days) will be audited for every 3-month period during the 1-year implementation period. The timing of the teaching sessions of the breakthrough project will be synchronous with the timing of the implementation steps (Fig. 2). Although the effectiveness of both strategies will be evaluated and compared every 3 months after every step or teaching session, the main goal of the study is to compare effectiveness at the end of the project using all patients collected during the year. Costs for the two implementation strategies will be calculated from hours and tariffs for the strategy delivery team (CBO expert, subject matter experts) as well as all costs for surgeons, anaesthetists, and nurses attending implementation-related activities, including time, travel, and conference expenses. Furthermore, the costs of materials will be calculated. Additional costs of the audit database will be calculated as well, as this is an essential part of the implementation strategies. Standardised forms will be developed for the measurement of activities, materials, and expenses associated with implementation [34]. Those forms will be filled in by members of the implementation team at each site and will provide information for the economic and process evaluation of the quality mprovement. Qualitative data regarding the process evaluation will be derived from extensive notes of all contacts with each hospital and during the educational sessions. Minutes will be taken by at least two members of the expert or local implementation team.

### Sample size

With the support of the DGOG, we expect to include the majority of Dutch hospitals and all patients that will be exposed to major gynaecological surgery during the implementation year. Approximately 100 patients undergo surgery per hospital per year. We do not expect drop outs among patients as informed consent procedures and filling in questionnaires by patients is not needed. The history of adherence to the ERAS protocol in the Netherlands during the implementation year will be described, so this study is in principle not about statistics and sample size calculations. However, it may be still worthwhile to calculate what statistical differences we will be able to assess, taking the perspective that this sample can be seen as an estimate for the future health care or assuming that some hospitals will not participate as expected. The stepped implementation strategy is expected to be superior to the breakthrough strategy in improving perioperative care processes and reducing the length of hospital stay. Anticipating a total adherence of 50 % to the benchmark of length of stay of 5 days or less in the breakthrough hospitals versus 70 % adherence in the stepped implementation hospitals, we would need to randomise seven hospitals per arm, each including at least 60 patients during the whole study period. Sample size computation was based on an estimated intra-class correlation coefficient (ICC) of 0.06 in secondary care, a power level of 80 %, and a significance level (*α*) of 0.05. The intra-class correlation coefficient used to calculate the sample size was based on a study of Campbell et al. [35]. Although this study reported significantly lower ICCs for outcome variables compared to process variables, we have conservatively computed the sample size using the highest applicable ICC of 0.06 for secondary care. Using an inflation factor of 11 % to account for unequal cluster size yields a recruitment target of 67 patients per cluster. It is possible that no clinically relevant differences (<20 %) between arms could be found. In such a case, we expect the stepped implementation programme still to be superior from a financial perspective.

### Data analysis

#### Effect evaluation

Descriptive statistics (proportions, mean, and median) will be performed for process and outcome data sets. Differences between groups will be evaluated using independent sample *t*-test for numerical variables and chi-square test for categorical variables. Since patients are nested within hospitals, implementation effects will be analysed using linear or logistic mixed-effect model analysis for numerical or binary outcome measures, accounting for a random hospital effect. Since the four implementation periods can be considered as different (time) groups, this time variable will be included as a factor in the regression model. Besides, subgroup analyses will be performed to describe trends in implementation over time in more detail. Non-inferiority comparisons will be presented for outcome measures using 95 % confidence intervals. Two-sided *p* values ≤0.05 will be considered as statistically significant. Statistical analyses will be performed using SPSS® version 22 software (SPSS, Chicago, Illinois, USA).

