#### Economic evaluation and budget impact

The uncertainty as regards the cost-minimisation results will be quantified using bootstrapping techniques. Subgroup and sensitivity analysis will be performed to test for the robustness of results. An effectiveness analysis will be performed every 3 months after completing a learning session. Thus, we will be able to judge to what level of intensity the activities are worth the effort. Implementation costs and effectiveness (savings due to reduction in hospital stay) will be calculated for each period, as well as cumulative implementation costs and cumulative effectiveness. A budget impact analysis will be performed addressing the financial stream of consequences related to the uptake and diffusion of the ERAS programme to assess affordability [36]. The budget impact will depend on both the costs of both strategies and the effect in terms of hospital stay reduction as well as the current level of uptake of ERAS.

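### Two procedures are named for comparing the arms, one of which ignores hospital clustering, and the text does not say which one decides

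*Protocol article*

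**What the plan says.** The Design section makes the hospital the unit of randomisation. The Effect evaluation paragraph under Data analysis opens with descriptive summaries of process and outcome data, and then states: "Differences between groups will be evaluated using independent sample *t*-test for numerical variables and chi-square test for categorical variables".

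The following sentence names a second procedure: "Since patients are nested within hospitals, implementation effects will be analysed using linear or logistic mixed-effect model analysis". That model carries a random effect for hospital, and implementation period is added as a factor.

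One decision rule closes the paragraph, with no distinction between the two procedures: "Two-sided *p* values ≤0.05 will be considered as statistically significant".

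The Sample size section allows for clustering, using "an estimated intra-class correlation coefficient (ICC) of 0.06 in secondary care, a power level of 80 %, and a significance level (*α*) of 0.05". The Data collection section says that effectiveness will also be compared after each 3-month step, and that the main comparison uses all patients of the year. It names no test for either.

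**The concern.** An independent-samples t-test and a chi-square test take the patient as the independent unit. When hospitals are randomised, patients within a hospital resemble each other, and the variance of an arm difference is larger than these tests assume. The p values come out too small and the intervals too narrow.

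The sentence on these tests stands under Effect evaluation, directly after a sentence about process and outcome data. Elsewhere the article uses the word group for the trial arms. Read plainly, the sentence covers the outcomes, including the numerical primary outcome, nights in hospital after surgery.

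Two things are at stake. An unclustered p value could present ordinary variation between hospitals as superiority of one strategy, in a trial meant to choose a strategy for nationwide use. And with two p values available for one contrast and no stated priority, the choice between them can be made after the results are seen.

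**Working it through.** **Inputs, all from the Sample size section unless noted.** ICC 0.06; two-sided alpha 0.05; power 80 %; 50 % versus 70 % of patients meeting the 5-day benchmark; 7 hospitals per arm with at least 60 patients each; a target of 67 per hospital after 11 % inflation; about 100 patients per hospital per year; about 25 per 3-month period (Fourth implementation level).

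**Step 1: reproduce the plan's sample size.** Patients per arm without clustering (pooled variance, no continuity correction):

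n = [1.96·√(2·0.6·0.4) + 0.842·√(0.5·0.5 + 0.7·0.3)]² / 0.20² = 93

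Design effect (DE) at m = 60: 1 + (60 − 1)·0.06 = 4.54. Then 93 · 4.54 = 422 per arm, and 422 / 60 = 7.04 hospitals. The stated 7 × 60 = 420 reproduces, with power 79.8 %. Also 60 · 1.11 = 66.6, which rounds to 67. The plan therefore enlarges the sample about 4.5-fold for a correlation that the t-test and chi-square test ignore.

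**Step 2: type I error of a test that ignores clustering.** With no true difference, the naive standard error is too small by a factor √DE, so

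type I error = 2·[1 − Φ(1.96 / √DE)], with DE = 1 + (m − 1)·ICC.

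The number of hospitals does not enter this formula.

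| ICC | m = 60 | m = 67 | m = 100 |
|---|---|---|---|
| 0.06 (plan) | DE 4.54: 35.8 % | DE 4.96: 37.9 % | DE 6.94: 45.7 % |
| 0.04 (assumed) | DE 3.36: 28.5 % | DE 3.64: 30.4 % | DE 4.96: 37.9 % |
| 0.02 (assumed) | DE 2.18: 18.4 % | DE 2.32: 19.8 % | DE 2.98: 25.6 % |
| 0.01 (assumed) | DE 1.59: 12.0 % | DE 1.66: 12.8 % | DE 1.99: 16.5 % |

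For one 3-month period (m = 25) at ICC 0.06: DE = 1 + 24·0.06 = 2.44, error 21.0 %.

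**Step 3: check by simulation.** 20,000 null trials, 7 versus 7 hospitals of equal size, ICC 0.06. The chi-square test rejected in 35.2 to 36.1 % of trials at m = 60 and in 45.8 % at m = 100. The t-test rejected in 35.4 % and 46.0 %. A t-test on the 14 hospital means, which respects the clustering, rejected in 5.0 to 5.3 % across the cluster sizes tried.

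**The case against.** The strongest answer is that clustering is already handled where it matters: "Since patients are nested within hospitals, implementation effects will be analysed using linear or logistic mixed-effect model analysis". On this view the t-test and chi-square sentence belongs to the descriptive step before it, and inference comes from the model. That reading is plausible, and it limits the point. A reader might infer that the trial's effect analysis carries a 36 to 46 % false-positive rate. The document does not support that: the rate applies only if an unclustered p value is used to infer an arm difference, and the plan does not say that it will be. What the objection does not do is remove the ambiguity. The tests are not restricted to description, the paragraph concerns process and outcome data, and the 5 % rule is general.

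A second objection is that the size is an upper end: "we have conservatively computed the sample size using the highest applicable ICC of 0.06 for secondary care", and the plan reports lower ICCs for outcome than for process variables. This stands, and it is why lower values are shown. Every one of them still gives more than twice the nominal 5 %.

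Third, if the sentence meant only patient characteristics, a false positive would not favour a strategy. That is true. The tests would still ignore nesting, but the consequence for the trial's conclusion would fall away. The text does not confine the sentence in this way.

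Two further inferences should be resisted. A reader might conclude that the mixed model will itself over-reject because few hospitals are randomised. The article does not state the model's reference distribution, which is commonly left to the analysis plan. A reader might also conclude that the cost analysis resamples patients rather than hospitals. The article says only "The uncertainty as regards the cost-minimisation results will be quantified using bootstrapping techniques" and does not give the resampling unit. Neither is an error in the document.

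**Conclusion.** The point holds in a limited form. The Effect evaluation paragraph sets an unrestricted, unclustered procedure beside a clustered one, under one significance rule, without saying which decides. Used to infer a year-end arm difference, the unclustered tests have a two-sided type I error of 35.8 % at 60 patients per hospital, 37.9 % at 67 and 45.7 % at 100, at the plan's upper-end ICC of 0.06. At assumed ICCs of 0.01 to 0.02 the range is about 12 to 26 %. The mixed model's error rate is not in question here.

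The figures assume equal hospital sizes, one common within-hospital correlation and a normal approximation, which the simulation supports.

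**What to change.** Delete the t-tests and chi-square tests for comparisons between arms, and keep only descriptive summaries by arm. State that every between-arm estimate, confidence interval and p value, including those of the 3-monthly comparisons, comes from the linear or logistic mixed model with the random hospital effect.

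This changes wording only and needs no new data or hospitals. The article reports that data collection was in its last phase at submission, so the rule could be settled before the final analysis. The price is wider intervals and larger p values than the unclustered tests would give, and the sample size already allows for this through its design effect.

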## Methods

### Design

The present study is a non-blinded cluster randomised controlled trial with two arms comparing an innovative stepwise implementation approach to the existing generic breakthrough approach. After approval to participate, a retrospective baseline measurement of 30 patients will be performed to assess current perioperative practice. Cluster randomisation will be applied at the hospital level and will take place after all retrospective measurements have been completed. Randomisation will be executed at the central level by an independent statistician of Maastricht University. The hospitals will be allocated to the intervention (stepped strategy) or to the control group (breakthrough strategy) (Fig. 1). After 1 year, the implementation process will be ended by a final sustainability meeting for both groups. We assume differences in uptake of innovations between the high-volume tertiary care hospitals and their affiliated regional hospitals. Stratified randomisation will be used to prevent unbalanced intervention groups with respect to tertiary status or not.

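### The effect model stated in the article has no patient-level prognostic term, so precision may be lost and chance case-mix imbalance stays uncorrected, although the randomised comparison remains valid

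*Protocol article*

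**What the plan says.** All references are to the protocol article.

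- **Model** (Data analysis, Effect evaluation): "implementation effects will be analysed using linear or logistic mixed-effect model analysis for numerical or binary outcome measures, accounting for a random hospital effect". Of the four implementation periods the section says that "this time variable will be included as a factor in the regression model". No other model term is named.
- **Outcome** (Outcome measures, Effect evaluation): "The primary outcome measure is length of hospital stay, defined as the number of nights that a patient stayed in hospital after surgery".
- **Population** (Patients): women "scheduled for elective abdominal surgery for diagnosis and/or treatment of (suspected) ovarian, endometrial, or cervical cancer". The section adds: "No specific exclusion criteria will be applied".
- **Data** (Data collection): "Patient characteristics, process indicators, and outcome measures" are audited every three months during the implementation year. The characteristics are not listed.
- **Balance by design** (Design): "Stratified randomisation will be used to prevent unbalanced intervention groups with respect to tertiary status or not". The reason given is an expected difference in uptake between tertiary and regional hospitals, not a difference in patients.
- **Number of clusters** (Sample size): "we would need to randomise seven hospitals per arm, each including at least 60 patients during the whole study period".

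**The concern.** Length of stay is compared between two groups of hospitals whose patients are unselected within a broad indication. If stay depends on age or tumour site, and hospitals differ in these, part of the between-hospital variance is case mix. With few hospitals per arm, that variance dominates the standard error of the arm effect, and randomisation cannot be relied on to even out patient mix.

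Stratifying by tertiary status helps only with differences that follow that divide. The Professionals section refers to regional hospitals authorised to perform major ovarian surgery. Case mix may therefore also vary among regional hospitals, where the stratification gives no protection.

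Two things are at stake. One is precision in a design with no spare power. The other is the interpretation of the estimate actually obtained: a chance difference in case mix could resemble a strategy effect or hide one. The economic evaluation converts reduced stay into savings and ranks the strategies by net cost, so the same chance shift would carry into the economic conclusion.

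**Working it through.** **1. The plan's own figure.** Inputs from Sample size: 50 % versus 70 % staying 5 days or less, ICC 0.06, 80 % power, α 0.05 (two-sided, from Data analysis), 60 patients per hospital.

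- Individually randomised size: 93 per arm (pooled variance, no continuity correction).
- Design effect: 1 + (60 − 1) × 0.06 = 4.54.
- Hospitals per arm: 93 × 4.54 / 60 = 422.2 / 60 = 7.04, stated as 7. With unpooled variance: 90.26 × 4.54 / 60 = 6.83, rounded up to 7.
- Inflation: 60 × 1.11 = 66.6, stated as 67.

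The figure reproduces. Power at 7 × 60 per arm is 79.8 %.

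**2. Gain on the 5-day benchmark.** The variance of the arm difference is proportional to ICC × (1 − b) + (1 − ICC) × (1 − w) / 60. Here b and w are the *assumed* shares of between- and within-hospital variance that case mix explains.

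| b | w | SE ratio | Power |
|---|---|---|---|
| 0 | 0 | 1.00 | 79.8 % |
| 0 | 0.10 | 0.99 | 80.6 % |
| 0 | 0.20 | 0.98 | 81.5 % |
| 0.10 | 0.10 | 0.95 | 83.8 % |
| 0.25 | 0.10 | 0.88 | 88.6 % |
| 0.50 | 0.10 | 0.76 | 95.7 % |

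If case mix explains only within-hospital variance, the gain is 0.8 to 1.7 power points. It becomes material only if case mix explains a sizeable share of the between-hospital variance. These are normal approximations. A t reference with 12 degrees of freedom gives about 74 % unadjusted power, so the comparison between rows is more informative than the levels.

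**3. Gain on nights in hospital.** The article gives no SD for stay. *Assumed*: total SD 4 nights; a longer-stay tumour group (say ovarian) making up 0.4 of patients on average; a difference D of 2 to 4 nights; SD s of that group's share between hospitals of 0.10 to 0.15. From the document: ICC 0.06 and 7 × 60 per arm.

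- Total variance is 16: between 0.06 × 16 = 0.96, within 15.04.
- Unadjusted SE = √[(2/7)(0.96 + 15.04/60)] = √[(2/7) × 1.211] = 0.59 nights.
- Adjustment removes D²s² between hospitals and about D² × 0.4 × 0.6 within. Case mix alone contributes an SE of D × s × √(2/7).

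| D | s | SE from case mix | Remaining between + within/60 | Adjusted SE | Variance ratio |
|---|---|---|---|---|---|
| 2 | 0.10 | 0.11 | 0.920 + 0.235 = 1.155 | 0.57 | 0.95 |
| 3 | 0.15 | 0.24 | 0.758 + 0.215 = 0.972 | 0.53 | 0.80 |
| 4 | 0.15 | 0.32 | 0.600 + 0.187 = 0.787 | 0.47 | 0.65 |

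The reduction in variance is therefore about 5 %, 20 % and 35 %. The last row requires tumour site alone to explain 0.36 / 0.96 = 37.5 % of the between-hospital variance.

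**4. Size of a chance shift.** With a mean share of 0.4 and no credit for stratification, the 95 % range of the shift in mean stay is ± 1.96 × D × √[(2/7)(s² + 0.24/60)].

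- D = 1, s = 0.05: ± 0.08 nights.
- D = 3, s = 0.20: ± 0.66 nights.

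These shifts are already part of the sampling variation covered by the unadjusted standard error.

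**The case against.** **Covariates are usually listed elsewhere.** A journal article condenses the full protocol, and a covariate list is often left to that document or to the analysis plan. Nothing in the article says that the named terms are the only ones. This stands as a limit on the claim: it concerns the model *stated in the article*. If a prespecified list already exists, citing it settles the point. The objection does not remove the point, because the article does state model terms and none is a patient factor.

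**There is no validity problem.** A reader might infer that omitting case mix biases the comparison or invalidates the test. The documents do not support that. Hospitals are randomised, and the random hospital effect brings case-mix differences between them into the standard error. An unadjusted primary analysis is a legitimate choice.

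**The premises are partly inferred.** A reader might also take it that stay differs widely by tumour site, or that tumour site is collected and then ignored. Neither is established. The article gives no stay by tumour site and no spread of tumour mix between hospitals. Tumour site is not named as a recorded field; eligibility merely makes it likely.

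**The calculated gains are generous.** They give no credit for stratification by tertiary status. They are also measured against a model without stratum or baseline terms, which could absorb some of the same variance. Seven hospitals per arm is the calculated requirement, and the article expects most Dutch hospitals to join. All of this stands, and it is why the size is given only as a range under stated assumptions.

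**Conclusion.** The point holds as an avoidable inefficiency in the stated model, not as a flaw in its validity. The random hospital effect and period factor leave any prognostic patient information unused. The cost is possible loss of precision, and an estimate of stay and savings that is not corrected for whatever case-mix imbalance occurs.

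The article does not supply the inputs needed to fix the size. It may be negligible. Under the assumed SD, tumour-group difference and between-hospital spread, it is a 5 to 35 % lower variance of the arm effect, and less where stratification already balances case mix. Only the ICC and the 7 × 60 layout come from the document.

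**What to change.** Before the final analysis:

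- Prespecify a short set of preoperative patient-level fixed effects in both the linear and the logistic mixed models: age and, where recorded, the tumour site suspected before surgery.
- Exclude anything the implementation strategy could change, such as analgesia or catheter use.
- Report the model without these terms as a sensitivity analysis.
- Use the adjusted difference in stay in the savings calculation, or show the savings both ways.

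Timing matters. The trial is not blinded, and Trial status places it in the last phase of implementation and data collection. Covariates chosen after the arm results are seen would carry little weight.

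The cost is small: a few model terms, which as patient-level factors use no hospital-level degrees of freedom. The sponsor must confirm that tumour site is in the audit database and state how missing covariate values are handled. In the logistic model the adjusted odds ratio is conditional on the covariates, so it can differ from the unadjusted one even without imbalance. The report should say so.
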